### Randomization and blinding

Following the informed consent and baseline evaluations, participants at each center will be locally randomized to the tDCS, tACS and placebo groups in a 2:2:1 allocation ratio, giving more weight to the active interventions. A staff member who is not involved in any study procedures will be responsible for creating the randomization list, generated by an automatic web-based randomization program from GraphPad Prism, and monitoring it during the study. The number of participants in the sham group was planned as half of those receiving tDCS or tACS. This 20% sham allocation was decided upon on account of it being the smallest and statistically correct number of patients that can stay without treatment. Given prior studies in populations with chronic pain, which showed clinically relevant remission of symptoms after tES treatments, we expect a positive effect of the technique in our trial [11]. The corresponding 20% of the sample is sufficient to achieve an analysis with sufficient statistical power. Therefore, for ethical reasons, we are keeping the size of the untreated group to a necessary minimum given our sample size.

The study will be triple-blinded, as the patient and caregiver, the study clinician and/or interventionist, and the evaluator will be blinded to the group assignment until the completion of the trial. The NeuroConn Data analysis will also be conducted in a blinded manner. The device used for the tES intervention (DC-STIMULATOR MOBILE, neuroConn GmbH, Ilmenau, Germany) allows complete blindness. Only the research members in charge of generating the randomization list will have access to the patient’s intervention status. The success of blinding will be measured at the end of the intervention by asking the patients what type of stimulation they think they received.

Unblinding will take place once recruitment and subsequent data analysis are completed. However, the coding system includes a mechanism that allows rapid identification of the treatment procedure in a medical emergency such as (1) in case of administration of an incorrect stimulation dose that could endanger the patient; (2) cases in which further treatment of the patient depends on knowledge of the treatment provided by the medical device;, and (3) in case of serious adverse events.

### Interventionist and assessor training

Study staff and investigators received intensive training in the methods through specialized training workshops (both on-site and online) focusing on the home-based application of tES and use of QST and EEG systems to ensure standard protocols across study sites. Training materials include videos and written manuals for study staff, as well as for patients and caregivers.

## Transcranial electrical stimulation treatment

Home-based tES will be applied during 20 min per session for 15 consecutive days via a DC-STIMULATOR MOBILE stimulator (neuroConn GmbH, Ilmenau, Germany) with a proprietary neuroConn headgear (Knitted tES-CAP, neuroConn GmbH, Ilmenau, Germany) comprising two rectangular textile electrodes of 35 cm² and 25 cm² for tDCS and tACS montages. The caps are of flexible textile material, in five sizes matched different head shapes with respect to circumference and height, and include ear openings and a Velcro chin strap to ensure a comfortable fit with adequate contact between the scalp and the electrodes [45, 46]. The textile electrodes comprise three layers surrounded by diffusion barrier of silicon yarn. The knitted fabric of the bottom layer contains a conductive silicone thread. The middle layer is formed by sponge material providing an electrolyte reservoir for 0.9% isotonic saline solution. The top layer of the cap knitted fabric holds sockets and studs of snap fasteners and red or blue-colored threads indicating the anode and the cathode respectively. Electrodes maintained contact with the scalp via 0.9% isotonic saline-soaked sponges. The press-stud electrode cables clipped on the snap fastener studs in the Knitted tES-CAP connect to the single button-controlled DC-STIMULATOR MOBILE.

The stimulation device is categorized as a Class IIa medical device with manageable risks and approved treatment effects, according to the European guidelines on medical device regulation [47, 48]. All devices will be calibrated, programmed, and checked by the manufacturer, neuroConn GmbH before the start of the study. The pre-programmed tES device stores the patient’s treatment parameters accordingly, to allow for home-based treatment.

*Anodal tDCS* The anode will be placed over the left M1 (C3, according to the 10–20 EEG system) and the cathode will be placed over the right orbito-ocular region (FP2). For the anodal tDCS, a constant current of 2 mA (20 min) with 15 s ramp-up and 15 s ramp-down at the beginning and the end of the stimulation period respectively was applied. The sham tDCS profile will constitute a 15 s direct current ramp-up to 2 mA, 15 s ramp-down to 0.05 Ma, 1130 s of 85 Hz sinusoidal current at 0.05 mA, at the beginning and end of the session, validated in [49]. *tACS* The electrodes will be placed in an F3-F4 montage over the frontal region targeting the DLPFC. A 10 Hz alternating current of 2 mA (peak-to-peak amplitude) will be applied for 20 min, with 15 s ramp-up and 15 s ramp-down. Participants in the sham group will have the same electrode montage as the tES protocols, with a ratio of tDCS to tACS montages 1:1. The sham sham tACS profile will constitute a 15 s 10 Hz sinusoidal alternating current ramp-up to 2 mA, 15 s ramp-down to 0.05 mA, and 1130 s of 85 Hz sinusoidal current at 0.05 mA, at the beginning and end of the session, validated in [50]. *Impedance quality* will be ≤ 15kΩ to ensure proper stimulation of the cortex. The application of tES follows consensus standards in the field, based on previously published guidelines [11, 51].

During each intervention session, participants will be instructed to assume a comfortable position (sitting or lying) and to rest (not to be involved in cognitive tasks or watching TV, but not sleep).

Each participant will receive 15 intervention sessions. The first tES session will take place in the study center (Visit 3), where the patient and/or caregiver will be trained by a researcher and/or clinical staff to operate and use the tES device and accessories. The patient will receive a tutorial handbook with a complete explanation of the procedures for stimulation and will also have access to an online video tutorial in their mother tongue. All supporting material will be available in the native language of the corresponding country. Then, the 14 stimulation sessions (two weeks) will be administered by the caregiver in the patient’s house or self-administered by the patient under remote supervision of the researchers.

The researcher/medical staff will be responsible for remotely authorizing and monitoring the daily stimulation session through the PAINLESS platform. In case of emergency, the patient or caregiver should call the numbers given them to the training session (medical emergency and stimulation related emergency). At the end of the whole treatment (15 days), researchers will be able to see whether the sessions were carried out correctly (day, time, duration and further configuration settings of the stimulator) without affecting the blinding of the study. This information is stored in a log file generated by the stimulator and saved in the storage module of the stimulator. After treatment completion, the log file and the stimulation data (applied current, adjusted voltage and resulting impedance) will be uploaded to the PAINLESS platform. Only authorized research members will be granted access to the stimulation data. Patients will provide their daily NRS and complete the medicine intake diary using the online PAINLESS platform, which will define an additional access in a patient’s role.

## Assessments and measures

### Primary outcome

The primary outcome will be self-reported cancer pain intensity, assessed by using the 11-point NRS [0: no pain due to cancer; 10: intolerable pain due to cancer] [52, 53]. The cancer pain intensity will be reported daily on the PAINLESS platform for 45 days (15 days pre-treatment, 15 days during, and 15 days post-treatment, recorded about the same time of the day). In addition, it will be reported at T0, T1, T2 and T3 visits with a recall period of 1 week. The reproducibility and cross-cultural validity of the NRS have been shown in chronic cancer-related pain, making it a reliable measure for pain assessment as a clinical outcome in many studies [54].

We will follow an intention-to-treat approach with missing data being imputed following the method that allows us to obtain the best adjustment.

### Secondary outcomes

#### Self-reported questionnaires

Patients will fill in a battery of scales and questionnaires at T0, T1 and T2, using the PAINLESS platform. At T3, only some of the scales will be delivered telephonically or online.

Pain and its dimensionsThe NRS for pain unpleasantness [0: not unpleasant at all; 10: maximum unpleasantness of pain] will be reported daily 15 days pre-, during, and post-treatment, similar to NRS for pain intensity, and assesses the impact of the intervention on the affective-motivational dimension of pain. NRS will also be assessed at T0, T1, T2, and T3 visits with a one-week recall window. This score has been shown to exhibit good sensitivity as well as discriminant and convergent validity and sensitivity to change [55].The NRS for the interference of cancer-related pain in daily life during the last day [0: no interference at all; 10: maximum interference] will be reported daily 15 days pre-, during, and post-treatment, to address the extent to which cancer pain hinders the individual’s engagement with their daily activities.The 9-item Brief Pain Inventory (BPI) assesses pain holistically, including the history, location, severity, and impact. The Pain severity (Items 3 to 6) and the Interference components (Item 9) of the BPI will be used as outcome variables [56]. Higher scores indicate higher severity.The 13-item Pain Catastrophizing Scale (PCS) tests the level of pain catastrophizing in patients, defined as exaggerated negative cognitive-affective response to actual or anticipated pain experiences [57, 58]. Higher scores reflect higher levels of catastrophic thinking. The overall score will be calculated (range 0–52), with a total score of >30 indicating a clinically significant level of pain catastrophizing. High levels of pain catastrophizing in cancer patients with chronic pain have been associated with reduced quality of life and higher levels of pain, fatigue, and sleep impairment [59].Quality of lifeThe total score of the 36-Item Short Form Survey (SF-36) (Ware, 2000), a commonly used and validated questionnaire to assess the quality of life in different populations of cancer patients and across countries [60–63], will be used to determine the quality of life of participants (range 0–100). Higher scores indicate higher quality of life.The European Quality of Life 5 Dimensions 3 Level Version (EQ-5D-3 L) instrument [64, 65], a valid and reliable questionnaire in both European and non-European cancer patients [66–68], will also be used to measure health-related quality of life.Composite scores of these two questionnaires will be also investigated.FatigueThe 21-item Modified Fatigue Impact Scale* (*MFIS) [69, 70] will be administered to assess the level of fatigue, a debilitating consequence of cancer, affecting over half of cancer patients [71, 72]. The scale accounts for the physical, emotional, and social components of fatigue and the overall score ranges from 0 to 84, with higher scores representing higher levels of fatigue.Sleep qualitySleep fragmentation is one of the most distressing symptoms impeding the quality of life of cancer patients throughout all stages of the disease and all phases of treatment, with a prevalence of 60.7% of sleep disturbance [73]. The 12-item Sleep Scale from the Medical Outcomes Study (MOS) scale [74], a frequently used subjective assessment of sleep disturbance in patients with malignant or chronic illnesses [75–79], will be used to assess sleep quality of patients. The aggregated MOS score (range 11–71) will be calculated, with higher scores representing greater sleep dysfunction.Performance statusThe 6-point scale Eastern Cooperative Oncology Group (ECOG) scale [80] (0: fully functional and asymptomatic, 1: symptomatic, fully ambulatory, 2: symptomatic, in bed or chair < 50% of the day, 3: symptomatic, in bed or chair >50% of the day, 4: bed- or chair-ridden, 5: dead) will be administered to assess how the patient’s disease is progressing and evaluate how the illness affects their abilities of daily living, including self-care.Psychological impairmentThe 9-item Patient Health Questionnaire (PHQ-9) [81, 82], a self-administered instrument for screening, monitoring, and assessing the severity of depression, will be used to assess the depression level of the participants. Higher scores are associated with higher levels of severity.The 7-item Generalized Anxiety Disorder (GAD-7) scale [83] will be implemented to assess the level of anxiety in patients, with higher scores indicating higher levels of anxiety.Cognitive functioningCognitive complaints are one of the most common consequences of cancer and its treatment, and have a negative impact on the well-being of patients. The 20-item *ONCOFOG (OFQ) questionnaire* will be used to assess the cognitive complaints (including different domains such as attention, memory, etc.).Subjective improvement and satisfactionThe participants will fill in an ad-hoc questionnaire. The instrument will aggregate all the physical and emotional functioning, side effects etc. into an overall measure of their perception of the advantages and disadvantages of the treatment received.Medication diaryThe participants will record their daily use of medication, including type and dose, in a medication diary throughout the study.Socioeconomic statusA socio-economic variables questionnaire will be administered to explore the financial costs of cancer (direct and indirect, medical and non-medical costs) for patients in home care. Its analysis will enable assessment of the socioeconomic cost/benefit associated with the tES treatment.

The following questionnaires will be completed on the PAINLESS platform by the relative/caregiver in charge of assisting the patient in day-to-day life and supporting the patient in conducting the home-based tES:

The 12-item Zarit Burden Interview (ZBI), a specific instrument for the relatives/caregivers of cancer patients will be used to assess the burden (stress and negative feelings) associated with the caring task [84].The SF-36 will be filled in to assess the impact of the intervention on the quality of life of care providers [85]. This is also an indirect measure of the patient’s autonomy.A socio-economic variables questionnaire to explore the economic costs associated with ambulatory and home-based care for patients with cancer. The analysis of this questionnaire will serve to assess the costs and benefits associated with the tES intervention, from the side of the relatives.

#### Psychophysical and neurophysiological measures

##### Quantitative sensory testing

Graded thermal stimulations will be applied to the skin by the TCS II thermal contact stimulator (QST.Lab, Strasbourg, France), which comprises several micro-Peltier thermo-electric elements that achieve very steep temperature ramps (i.e., up to 300 °C/s). The thermode has a total stimulation surface of 4.5 cm^2^. That way, the time required to estimate the pain threshold with this method is less than 2 minutes per skin area. We can, thus, easily activate small, thermal nociceptive nerve fibers conveyed by the spinothalamic tract. These properties yield a cost-effective test with reduced test-retest variability, fewer safety precautions, and a lower burn risk than conventional laser stimulators. The perceived pain intensity of ongoing thermal stimulations will be assessed using an 11-point NRS (0: no pain; 10: worst pain imaginable). The patients will be seated during the experiments, with eyes open. Room temperature will be controlled.

The QST procedure is detailed below in order of application and summarized in Fig. 1.

**Fig. 1 Fig1:**
[figure not shown]
Timeline for each assessment visit including measures of quantitative sensory testing and electroencephalography. TSP, Temporal Summation of Pain; CPM, Conditioned Pain Modulation; HPT, Heat Pain Threshold; CDT, Cold Detection Threshold; CPT, Cold Pain Threshold; OA, Offset Analgesia; EEG, electroencephalography; rsEEG, resting state EEG; CHEP, Contact Heat Evoked Potential

FamiliarizationParticipants undergo a short training to familiarize themselves with the heat stimuli.
aHeat pain: 1 stimulus of 45 °C for 5s. Ramp-up and ramp-down: 170°C/s.bCold pain: 1 stimulus of 0 °C for 5s. Ramp-up and ramp-down: 170°C/s.
Pain5 determinationPain5 is defined as the temperature resulting in pain intensity ratings of 5 on the NRS scale, which will be determined for the temporal summation of pain (TSP) and the conditional pain modulation/offset analgesia (CPM/OA) procedures separately. The determination process will be repeated twice for each. The mean of the temperature yielding a pain intensity self-report of 5 will be calculated for each of the TSP and CPM/OA determinations. For determining the Pain5 for both TSP and CPM/OA, the starting temperature is set at 45 °C. If the pain intensity rating is > 5/10, we will reduce the temperature by −1 °C (i.e., 44 °C) for the following stimulation. Conversely, if the pain intensity rating is lower than 5/10, we will increase the temperature by + 1 °C (i.e., 46 °C) for the following stimulation. This process is repeated until an NRS of 5 is achieved. The inter-stimulus interval is 5s. The difference in the procedures is a stimulation duration of 0.5 s and 10 s for TSP and CPM/OA respectively.Temporal summation of painTSP refers to the increased pain perception from repetitive noxious stimuli resulting from wind-up, whereby spinal neurons exhibit enhanced firing owing to repetitive input to the C-fibers [86, 87]. The test-retest reliability of thermal TSP has been previously validated, supporting its implementation as a consistent behavioral correlate of central sensitization [88, 89]. Initially, a single stimulus at the determined Pain5 for TSP is applied, with a pulse duration of 0.5s and a ramp-up and -down of 170 °C/s in the dominant volar forearm. The participant is asked to rate the pain intensity for this stimulus, with a maximum of 10 s to rate the pain. Then, 10 stimuli at the determined Pain5 for TSP will be applied with a pulse duration of 0.5s, a ramp up and down of 170 °C/s, and an inter-stimulus interval of 0.5s (i.e., stimulus onset to onset interval of 1 s and stimulation frequency of 1 Hz). The participant is asked to rate the pain intensity for the last of the stimuli in the sequence. The TSP index will be calculated as the normalized difference in pain intensity ratings between the initial single stimulus and the last pulse of the 10-stimulus sequence [90].Conditioned pain modulationCPM, known as the ‘pain inhibits pain’ phenomenon, appears when the presence of a second noxious stimulus (conditioning stimulus) reduces the pain perceived from an initial noxious stimulus (test stimulus) [91]. CPM has been described as the behavioral correlate of diffuse noxious inhibitory control, a phenomenon whereby inputs from peripheral C-fibers lead to diffuse inhibition from the brainstem of incoming noxious stimuli mediated by heterotopic C-fibers [42, 91, 92]. First, the test stimulus at Pain5 for CPM/OA is applied for 10 s, with a ramp-up and -down of 170 °C/s in the dominant volar forearm. The participant is then requested to rate the pain intensity perceived. Subsequently, the participant is asked to place the palm of their non-dominant hand on the cold plate. After 20 s, they are asked to rate their perceived pain. At 30 s after placing the palm on the cold plate, the test stimulus is applied again and the pain rating is measured. As soon as the evoked pain intensity for the second test stimulus application (conditioning stimulus) has been produced, the palm of the non-dominant hand is removed from the cold plate. The stimulation site for applying the test stimulus will be slightly moved for each application to avoid thermal receptor habituation. The CPM index is calculated as the normalized difference between the evoked pain ratings for the test stimulus before and after the application of the conditioning stimulus [93].Thermal pain and detection thresholdsThe heat pain threshold (HPT), the cold detection threshold (CDT), and the cold pain threshold (CPT) will be determined using the previously described methods of limits [39]. For each threshold, three trials will be performed with 5 s inter-trial intervals. For the HPT and CPT, the participant will be asked to press the response button as soon as a hotness or coldness perception becomes painful respectively. For the CDT estimation, the participant is asked to press the response button as soon as coldness is perceived. The stimulation site will be the dominant volar forearm and will be moved slightly between each stimulation to avoid habituation of the thermal receptors. Temperature will change (i.e., increases for HPT, and decreases for CDT and CPT) at a rate of 1 °C/s. Between HPT and CPT trials (i.e., as soon as the response button is pressed) temperature returns to the baseline level at a rate of 8 °C/s, while for CDT it returns at a rate of 170 °C/s. To determine the threshold, the arithmetic means of the temperature at the response button press across the three trials for each threshold will be used as the corresponding threshold estimation.Offset analgesiaOA is defined by a profound decrease in perceived pain intensity on a slight decrease in temperature during noxious thermal stimulation, which is more disproportionate than expected from the rate of temperature reduction [94, 95]. Unlike CPM which relies on solely central mechanisms, OA is mediated by both peripheral and central mechanisms [43]. CPM and OA activate distinct brain areas, engage different inhibitory processes in the central nervous system, and demonstrate no correlation between indices [96]. This protocol will require an electronic visual analogue scale (eVAS 0–10). Heat stimulation will be delivered to the dominant volar forearm. First, a familiarization step will be taken with the stimulation intensity set at the determined Pain5 for CPM/OA minus 2 °C, with a duration of 10s. Participants will be asked to use the eVAS device to rate the perceived pain intensity evoked by this stimulation. OA will be induced by applying the determined Pain5 temperature during 5 s, then Pain5 plus 1 °C for another 5 s, and then again, the Pain5 for 20s. A constant heat stimulus with the pre-determined Pain5 for 30 s will be used as a control stimulus. It will be applied either before or after the OA stimulus according to a counterbalancing scheme. Patients will rate their pain level continuously on the eVAS during both OA and control stimulations. The OA index is calculated as the normalized difference in pain intensity ratings during the last 20 s of the OA trial and the control trial.The baseline temperature will be set at 32 °C for Pain5 determination and TSP, CPM, HPT, CDT, CPT, and OA measures.

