
##### Concurrent EEG-QST measures]

EEG measures will be recorded using a portable, adaptable, and simple-to-use MENTALAB Explore + recording system developed and adapted to clinical use (Mentalab GmbH, Munich, Germany). EEG signals will be acquired by 32 electrodes mounted in an elastic cap and arranged according to the international 10–20 system. The EEG signal will be amplified and digitized using a sampling rate of 250 Hz, and the reference will be placed at CPz. Impedances will be kept under 10kΩ for all electrodes.

Firstly, resting state electroencephalography (rsEEG) will be recorded for 5 min with participants maintaining their eyes closed. The participant will be instructed to sit comfortably and relax letting their mind wander. Next, a second rsEEG recording will be performed, but with a cold noxious stimulus being applied to the palm of the dominant hand. At the end of the test, the participant will be asked to report the average level of pain perceived during the 5 min. The intensity of the cold pain stimulus must be between 3 and 5/10 on the NRS during the whole recording. The timeline for the concurrent measures is also illustrated in Fig. 1.

Finally, we will record Contact Heat Evoked Potentials (CHEPs) using concurrent QST-EEG.

CHEPs, mediated by Aδ fibers, are a neural correlate of nociceptive processing and dysfunction in humans [44, 97, 98]. CHEP parameters can inform researchers about the maladaptive neuroplastic changes in chronic pain patients, though this is not yet characterized in cancer patients [99]. We will apply 25 stimuli at 60 °C with a duration of 0.3 s and ramp-up and -down of 170 °C/sec, with an inter-stimulus interval of 10 s, to minimize saliency and startle responses. EEG will be simultaneously recorded. The baseline temperature will be 32 °C. If the stimulus is very painful, the temperature will be reduced by −1 °C. This process can be repeated until 55 °C is reached. At the end of the test, the participant will rate how painful the stimuli sequence was on average. The heat stimulation will be applied to the dominant volar forearm. The stimulation site will be moved slightly between each stimulus application to avoid habituation of the thermal receptors.

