In this study, we opted for self- or caregiver-administered and remotely supervised home-based tES over daily in-person stimulation at the study sites to improve the accessibility of the intervention to the patients. Persistent pain represents a significant barrier that can affect the ease of travel to health facilities and cause difficulties in accessing healthcare and treatments, with consequent economic and organizational impacts. The mobility limitations faced by chronic pain patients have brought about heightened awareness of the need to develop new health services based on digital technologies [114, 115]. Generally, it has been observed in patients with chronic pain that the improvement of monitoring through a telemedicine-oriented approach capable of guaranteeing continuous and effective communication with health care professionals can lead to a significant increase in the effectiveness of treatments [116]. Through a home-based approach both for tES as well as for daily clinical monitoring, we expect to reduce the direct and indirect healthcare and social costs, while improving the access to healthcare using e-health tools.

Beyond the greater accessibility of the treatment through home-based technology, our RCT overcomes commonly observed methodological limitations in previous studies testing the effectiveness of tES in chronic pain, including cancer-related pain. This study is a multicenter trial with a powered sample of 450 patients, addressing the underpowered sample sizes used in most studies [11, 19–21]. An important strength of our methodology is the study of the potential mechanisms underlying pain relief in cancer pain using QST and EEG measurements, in addition to self-reported questionnaires and ratings of pain and associated symptoms. Around 50% of studies in a systematic review reported sensory abnormities using thermal detection thresholds (CDT and HDT) and abnormal thermal pain processing using thermal pain threshold (CPT and HPT) [41] in cancer pain (mostly chemotherapy-induced neuropathic pain). The not yet studied QST-based conditioned pain modulation, temporal summation of pain and offset analgesia, and EEG-based CHEP measures will shed new light on the pro-nociceptive and anti-nociceptive mechanisms involved in tDCS- and tACS-induced analgesia in cancer pain patients.

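### The Pain5 titration can end only on a rating of exactly 5, and no rule covers patients whose ratings step over 5 or stay below it

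*Protocol article*

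**What the plan says.** The Pain5 determination, under Quantitative sensory testing in the protocol article, is described as a complete algorithm:

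- Start: "the starting temperature is set at 45 °C".
- Down: "If the pain intensity rating is > 5/10, we will reduce the temperature by" 1 °C.
- Up: "if the pain intensity rating is lower than 5/10, we will increase the temperature by" 1 °C.
- Stop: "This process is repeated until an NRS of 5 is achieved".

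Stimuli last 0.5 s for the TSP determination and 10 s for the CPM/OA determination, 5 s apart. Each determination is done twice and the temperatures are averaged. Heat pain in this section "will be assessed using an 11-point NRS (0: no pain; 10: worst pain imaginable").

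The result sets later stimuli: the TSP pulses, the 10 s CPM test stimulus, a 30 s constant control stimulus, and the OA trial, of which the article says "OA will be induced by applying the determined Pain5 temperature during 5 s, then Pain5 plus 1 °C for another 5 s", followed by 20 s at Pain5.

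No maximum number of stimuli, tolerance around 5, bracketing rule, upper temperature or procedure for a patient who never rates 5 is stated there or elsewhere in the article.

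**The concern.** A stopping rule that needs one exact value on a coarse scale, approached in fixed 1 °C steps, can fail in two ways.

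- **Stepping over 5.** A patient who rates 4 at one temperature and 6 at the next satisfies neither exit nor progress, and the rule sends them back and forth. If a 5 eventually comes by chance, Pain5 is whichever of the two temperatures happened to draw it.
- **Staying below 5.** A patient who keeps rating below 5 is moved up 1 °C each time, and the text gives no point at which this stops. The Introduction reports altered thermal detection and pain thresholds in cancer pain, and the Discussion adds: "Around 50% of studies in a systematic review reported sensory abnormities using thermal detection thresholds". Unusual responses to heat are therefore foreseeable in this population.

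At stake are the TSP, CPM and OA indices, which serve as candidate mediators in Aim 2 and as predictors of response in Aim 3, and the heat that participants receive while the titration runs and afterwards. QST is scheduled at T0, T1 and T2. If Pain5 is determined afresh each time, a patient undergoes 2 × 2 × 3 = 12 determinations.

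**Working it through.** The plan gives no figure for how often the titration converges, so there is none to reproduce. I applied the rule as written.

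**Inputs from the article:** start 45 °C; steps of 1 °C; stop at a rating of 5; integer ratings 0–10; 10 s stimuli (CPM/OA) with 5 s between them.

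**Assumptions (not in the article):** the rating at temperature T is 5 + s × (T − T5), plus noise, rounded to an integer and clipped to 0–10. T5 is the patient's true Pain5 and s is the slope in points per °C.

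**1. Stepping over 5, no noise.** A 5 is given only when T lies within 0.5/s of T5, a window 1/s °C wide. The titration visits whole degrees only. For s ≤ 1 the window always contains one. For s > 1 the share of patients whose window contains none is 1 − 1/s:

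| s (points per °C) | 1 − 1/s | never rate 5 |
|---|---|---|
| up to 1 | – | 0% |
| 1.5 | 1 − 0.667 | 33% |
| 2 | 1 − 0.5 | 50% |
| 3 | 1 − 0.333 | 67% |

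Example with s = 2 and T5 = 45.5 °C: at 45 °C the rating is 5 + 2 × (−0.5) = 4; at 46 °C it is 5 + 2 × 0.5 = 6. The rule alternates between the two.

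**2. The same with rating noise.** Simulation of 20,000 raters, T5 ~ N(46, 2) °C, noise SD 0.5 and 1:

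| s | more than 10 stimuli in one determination |
|---|---|
| 1.5 | about 3–7% |
| 2 | about 9–11% |
| 3 | about 20–31% |

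Nearly all of these runs end. In a second simulation with T5 spread evenly over 43–49 °C, the median at s = 2 was 4 stimuli and about 1% needed more than 20; at s = 3, 3–18% needed more than 20.

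**3. What a chance 5 does to Pain5.** In the example above, the recorded value is 45 or 46 °C, where the patient typically rates 4 or 6. Linear interpolation gives 45 + (5 − 4)/(6 − 4) × 1 = 45.5 °C, which is the true value.

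**4. Staying below 5.** Stimulus k is given at 44 + k °C, and with 10 s stimuli it ends 10k + 5(k − 1) s after the start. Stimulus 6 is at 50 °C and ends at 85 s; stimulus 11 is at 55 °C and ends at 160 s. This is what the written rule prescribes for such a patient. It does not say how many such patients there will be.

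**The case against.** The strongest reply is that a condensed article need not carry operating limits. It mentions written manuals, staff training, identical methods across sites and a coded stimulation program, any of which may hold a cut-off, and the device may impose one. This stands as far as the temperature limit goes: the article shows only that none is stated here. It does not dispose of the stopping rule, because the article gives that rule in full, with its own exit, and the rule as given need not converge.

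Several stronger readings are tempting but not supported:

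- **That the titration never ends for steep raters.** This holds only for perfectly consistent ratings. With modest noise nearly all runs end, and at slopes up to 1 point per °C even noise-free runs always do.
- **That patients will be driven to extreme temperatures.** The ladder in the working has no frequency attached. Under the N(46, 2) °C used for the simulation, 55 °C lies 4.5 SD and 60 °C lies 7 SD above the mean. That distribution is itself assumed and was not built to represent insensitive patients.
- **That the contact heat-evoked potential (CHEP) procedure sets a safety limit which Pain5 breaches.** There, "This process can be repeated until 55 °C is reached" is the floor of a downward adjustment from 60 °C for 0.3 s pulses, not a ceiling. Comparing exposure times with it measures Pain5 against a limit the article does not set.
- **That the protocol expects reduced heat sensation.** It says altered or abnormal, without a direction, and testing is moved away from primary pain sites.
- **That sites will improvise different stops.** This is possible, but the article promises common methods and training.

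The procedure is also the same in all three arms, so it does not by itself bias the randomised comparison.

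**Conclusion.** The point holds as a badly fixed measurement rule that should be corrected. It does not threaten the primary result. As written, the titration does not converge for consistent raters whose ratings pass over 5 in one step: 33%, 50% or 67% of them at slopes of 1.5, 2 or 3 points per °C. With noise of SD 0.5–1 the practical effect is about 3–7%, 9–11% or 20–31% of determinations running past 10 stimuli, and a Pain5 that depends on a chance rating. These sizes rest on assumed slopes, noise and T5 distributions; at shallow slopes the problem is small.

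For patients who stay below 5, the conclusion is limited to this: the document states no upper limit, and the value reached would carry over to longer stimuli, including one at Pain5 plus 1 °C. Only TSP, CPM, OA and participants' heat exposure are affected. The daily pain NRS, the thermal thresholds, resting EEG and CHEPs do not use Pain5.

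**What to change.** State a termination and non-convergence rule for Pain5, identical at all sites and in the stimulation code:

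1. When ratings on adjacent steps bracket 5, stop and take the interpolated temperature, T_low + (5 − r_low)/(r_high − r_low) × 1 °C.
2. Set a maximum number of stimuli per determination.
3. Flag patients who do not reach or bracket 5, say how their TSP, CPM and OA tests are handled, and analyse their Pain5 as censored.
4. State whatever upper temperature limit the sponsor, device and ethics approval already impose, and reconcile it with the 30 s control stimulus and the Pain5 plus 1 °C phase of OA. The value is for the sponsor to choose.

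Every run would then end at a 5, at a bracket or at a stated limit. The cost is a short procedural amendment and a change to the stimulation code. The downside is that a few patients will lack TSP, CPM or OA values. If determinations have already been made, record which rule each followed so that the two kinds of Pain5 can be told apart.
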